## Methods and analysis

### Trial approval and conduct

The trial is approved by the SingHealth Centralised Institutional Review Board (CIRB) (Ref: 2021/2738) and is registered on clinicaltrials.gov (NCT05568953). The trial sponsor is the Singapore General Hospital, Singapore, in collaboration with Duke-NUS Medical School, Singapore. The trial will be conducted at the SingHealth Investigational Medicine Unit, and carried out in accordance with the principles of the Singapore Good Clinical Practice guidelines and in compliance with the Helsinki Declaration. Written informed consent written will be obtained from all study participants before enrolment.

### Study population

A total of 70 flavivirus-naïve healthy adult volunteers meeting all inclusion criteria and non-exclusion criteria will be enrolled and recruited into the study.

#### Inclusion criteria

1. Healthy adults, male or female, aged between 21 – 45 years at the time of screening.2. Willingness to comply to study procedures and adhere to study schedule visits.3. Satisfactory baseline medical assessment as assessed by physical examination and a stable health status. The laboratory values must be within the normal range of the assessing site or show abnormalities that are deemed not clinically significant as judged by the investigator. A stable health status is defined as the absence of a health event satisfying the definition of a serious adverse event.4. Accessible vein for blood collection.5. Ability to provide informed consent.6. Female subjects of non-child bearing potential due to surgical sterilization (hysterectomy or bilateral oophorectomy or tubal ligation) or menopause. Post-menopausal subjects must have had at least 12 months of natural amenorrhea.7. Female subjects of child bearing potential with negative urine pregnancy tests on the day of screening and vaccination. Both male (if he has a partner of childbearing potential) and female subjects (of childbearing potential) must agree to use adequate and reliable contraceptive measures (e.g. spermicides, condoms, contraceptive pills) or practice abstinence for 10 days after vaccination.

#### Exclusion criteria

1. History of presence of cardiovascular, respiratory, hepatic, renal, gastrointestinal, neuropsychiatric, hematological, endocrine or immunosuppressive disorders that would be a risk factor when administered the study vaccines.2. Positive serum anti-dengue IgG by enzyme-linked immunosorbent assay (ELISA).3. Previous receipt of any yellow fever or Japanese encephalitis vaccines (including but not limited those that will be administered in this study).4. Previous history of yellow fever or Japanese encephalitis infection.5. Known allergy to JE-YF17D, YF17D or inactivated JEV vaccines or their components.6. History of severe food/drug/vaccine allergies e.g. angioedema, anaphylaxis.7. Known allergy to egg or egg products.8. History of thymus gland disease.9. Diagnosed with cancer or on treatment for cancer (with the exception of localized basal cell carcinoma) within 3 years prior to screening.10. Evidence of clinically significant anemia (Hb <10 g/dl).11. Blood donation exceeding >450mls in the past 3 months.12. Presence of acute infection in the preceding 7 days or presence of a temperature ≥ 38.0°C (oral or tympanic temperature assessment), or acute symptoms greater than of “mild” severity on the scheduled date of first dose.13. Pregnant or breast feeding women.14. Evidence of substance abuse, or previous substance abuse including alcohol.15. Participation in a study involving administration of an investigational compound (including investigational vaccines) within the past three months, or planned participation during the duration of this study.16. Receipt of anti-inflammatory drugs (such as NSAIDs or systemic steroids) in the past 7 days.17. Receipt of any licensed vaccine in the past 30 days before the first study vaccine dose.18. Any condition that, in the opinion of the investigator, would complicate or compromise the study or wellbeing of the subject.

### Study design

56 subjects will be randomized into 1 of 2 arms (Arm 1 and Arm 2) in a 1:1 ratio. These two arms will be double-blinded. Subjects in Arm 1 will receive JE-YF17D vaccine (IMOJEV^®^, Sanofi Pasteur) on Day 0, followed by YF17D vaccine (STAMARIL^®^, Sanofi Pasteur) on Day 28. Subjects in Arm 2 will receive YF17D vaccine on Day 0 followed by JE-YF17D vaccine on Day 28. A separate non-randomized non-blinded cohort of 14 subjects will be recruited into Arm 3. Subjects in Arm 3 will receive inactivated JEV vaccine (IXIARO^®^, Valneva) on Day 0 followed by YF17D vaccine on Day 28. **Table 1** summarizes the study design.

**Table 1 T1:** Study design.

Arms	Vaccination schedule	
	1^st^ vaccination (Day 0)	2^nd^ vaccination (Day 28)
Arm 1* (n=28)	JE-YF17D vaccine (IMOJEV^®^, Sanofi Pasteur)	YF17D vaccine (STAMARIL^®^, Sanofi Pasteur)
Arm 2* (n=28)	YF17D vaccine (STAMARIL^®^, Sanofi Pasteur)	JE-YF17D vaccine (IMOJEV^®^, Sanofi Pasteur)
Arm 3** (n=14)	Inactivated JEV vaccine (IXIARO^®^, Valneva)	YF17D vaccine (STAMARIL^®^, Sanofi Pasteur)

*Subjects (n=56) will be randomized in a double-blind manner to either Arms 1 or 2. **A separate cohort (n=14) will be recruited into Arm 3 in a non-randomized, single arm, open label design.

The rationale for these three study arms is as follows: Arm 1 will show the impact of a lower level of RNAemia induced by JE-YF17D vaccination (as compared to YF17D vaccination), and the resultant lower levels of virus-specific CD4+ and CD8+ T cells, would have on YF17D infection. In contrast, YF17D vaccination in Arm 2 would produce higher levels of RNAemia (as compared to JE-YF17D vaccination), and in turn higher levels of virus-specific T cells, thus likely resulting in greater suppression of JE-YF17D infection. The first vaccination in Arms 1 and 2 would provide the RNAemia response in the absence of virus-specific T cells, which would serve as a reference point to interpret the outcome of the second vaccination. For example, the level of suppression of JE-YF17D RNAemia will be the difference in RNAemia levels between subjects who received JE-YF17D as a second vaccination (Arm 2) compared to those who received it as a first vaccination (Arm 1), and similarly for YF17D vaccine. Arm 3 will serve as the control arm, as vaccination with inactivated JE vaccine should not produce any YF17D-specific T cell response.

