## Hypothesis and objectives

The overall goal of this study is to define a minimum quantitative threshold of T cells induced by vaccination needed to control subsequent infection, independent of antibodies. We will conduct an experimental study in healthy adult volunteers, leveraging on the immunogenic properties of the licensed live-attenuated yellow fever (YF17D; STAMARIL^®^, Sanofi Pasteur) and chimeric Japanese encephalitis-YF17D (JE-YF17D; IMOJEV^®^, Sanofi Pasteur) vaccines. These vaccines contain the same genomic YF17D backbone (13, 14): vaccination with either vaccine would likely produce T cell responses that, like other flaviviruses, are preferentially directed against the non-structural proteins encoded in their shared genomic backbone, and hence would cross-protect against each other (**Figure 1**). YF17D and JE-YF17D, however, encode different structural pre-membrane (prM) and envelope (E) proteins: vaccination with either would produce neutralizing antibodies protective only against that virus (15). Moreover, YF17D and JE-YF17D vaccination induce different levels of infection as determined by vaccine RNAemia (16, 17), and expectedly differing levels of innate immune responses, allowing us to evaluate how RNAemia and innate immune profile shapes T cell response. The properties of these two live-attenuated vaccines thus provide a unique opportunity to differentiate the role of T cell immunity from humoral immunity in controlling viral infection. In addition, we will also use the licensed inactivated Japanese Encephalitis virus (JEV; IXIARO^®^, Valneva) vaccine to control for the effects of cross-reactive anti-flaviviral antibodies, although we have not observed suppression of YF17D RNAemia from inactivated JEV vaccination (16). Overall, we hypothesize that a high CD4+ and CD8+ T cell response will reduce RNAemia upon challenge with a structurally heterologous virus, and correspondingly result in reduced magnitude of host response to challenge infection. The specific objectives of the study are as follows:

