### Randomization

For Arms 1 and 2, subjects will be randomized in a 1:1 ratio. 56 opaque sealed envelopes, each containing a study arm, will be randomly picked by a non-team member.

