### Study drug administration

As per manufacturer’s instructions, the administered dose of each reconstituted vaccine will be as follows:

1. YF17D (STAMARIL^®^, Sanofi Pasteur): 0.5 mls (4.0 - 5.8 log plaque forming units [PFU]) *via* subcutaneous injection2. JE-YF17D (IMOJEV^®^, Sanofi Pasteur): 0.5 mls (3 - 4 log PFU) *via* subcutaneous injection3. Inactivated JEV (IXIARO^®^, Valneva): 0.5 mls *via* intramuscular injection

In Arms 1 and 2, both JE-YF17D and YF17D vaccines will be administered by subcutaneous injection into the deltoid region of the left/right arm. The second (Day 28) vaccination will be delivered into the ipsilateral arm e.g. if the Day 0 vaccination is administered into the right arm, the Day 28 vaccination will also be administered into the right arm. In Arm 3, inactivated JEV will be administered by intramuscular injection into the deltoid region of the left/right arm and YF17D vaccine will be administered by subcutaneous injection into the deltoid region of the ipsilateral arm.

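### Arm 3, the control in the primary objective, is a separately recruited non-randomised cohort with no stated reason, although 28:28:14 is exactly a 2:2:1 randomisation of the same 70 subjects

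*Protocol article*

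**What the plan says.** The allocation of Arm 3 is stated outright. Study design says "A separate non-randomized non-blinded cohort of 14 subjects will be recruited into Arm 3", and the footnote to Table 1 repeats it: "A separate cohort (n=14) will be recruited into Arm 3 in a non-randomized, single arm, open label design". For the other two arms, "56 subjects will be randomized into 1 of 2 arms (Arm 1 and Arm 2) in a 1:1 ratio". The Randomization section provides for those two arms only: "56 opaque sealed envelopes, each containing a study arm, will be randomly picked by a non-team member". A footnote to Table 2 confirms that Arm 3 is not randomised. The total is 70 subjects (Study population).

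The role of Arm 3 is also clear. Study design says "Arm 3 will serve as the control arm, as vaccination with inactivated JE vaccine should not produce any YF17D-specific T cell response". Hypothesis and objectives says that the inactivated vaccine is used "to control for the effects of cross-reactive anti-flaviviral antibodies". The primary objective compares RNAemia after challenge between all three priming groups, including inactivated JEV, and Sample size calculation again calls Arm 3 the control group.

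The article gives no reason for leaving Arm 3 out of the randomisation. Data and statistical analysis names two-group tests for RNAemia (t-test or Wilcoxon rank-sum) and does not treat contrasts with Arm 3 differently from the randomised one.

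**The concern.** Two contrasts ask whether JE-induced, cross-reactive antibody alone alters YF17D RNAemia. One is Arm 1 versus Arm 3 after the Day 28 challenge: both were primed against JE and both then receive YF17D. The other is YF17D on Day 28 in Arm 3 versus YF17D on Day 0 in Arm 2, who have had no earlier study vaccine. Both cross the boundary between the randomised arms and the separate cohort.

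A difference in who enters Arm 3 would appear in these contrasts as if it were an effect of priming. It could create a difference or hide one. Differences in recruitment period, vaccine lot or assay run would act in the same way if they occur. The study aims at a T-cell threshold that is independent of antibody, so a control that serves this aim should be comparable by design where that costs no subjects.

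**Working it through.** **1. The plan's own sample size.** Inputs from Sample size calculation: effect 0.8 SD on the log10 scale, two-sided 5%, power 80%, drop-out 10%.
- n per group = 2 × (1.960 + 0.842)² / 0.8² = 24.5, so 25. The plan says 25.
- Power at 25 per group: 80.7% (normal approximation), 79.1% (noncentral t).
- 25 / 0.90 = 27.8, so 28. The plan says 28.

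The stated figures reproduce. They concern Arms 1 and 2 only. Arm 3 is set at 14 without a calculation.

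**2. Allocation ratio.** 28/70 = 0.4, 28/70 = 0.4 and 14/70 = 0.2, that is 2:2:1. Conversely, 70 × (2/5, 2/5, 1/5) = 28, 28, 14. One 2:2:1 list gives exactly the planned arm sizes.

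**3. Which contrasts are affected** (vaccination schedule in Table 1)

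| Contrast | Compares | Randomised? |
|---|---|---|
| Suppression of YF17D | Arm 1 Day 28 v Arm 2 Day 0 | yes |
| Suppression of JE-YF17D | Arm 2 Day 28 v Arm 1 Day 0 | yes |
| Same YF17D challenge, live v inactivated prime | Arm 1 Day 28 v Arm 3 Day 28 | no |
| YF17D after inactivated prime v YF17D as first vaccine | Arm 3 Day 28 v Arm 2 Day 0 | no |

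The first two are what the sample size is built on.

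**4. How much a non-causal shift would matter.** The shifts are assumptions, since the documents give none. For a two-sample t-test with no true effect and a systematic shift of d SD, the noncentrality is d / √(1/n₁ + 1/n₂) and the degrees of freedom are n₁ + n₂ − 2.
- 28 v 14: √(1/28 + 1/14) = 0.327, 40 df.
- 25 v 13: √(1/25 + 1/13) = 0.342, 36 df. The 13 applies the 10% drop-out to Arm 3 as well (14 × 0.9 = 12.6). The plan states that rate only for Arms 1 and 2.

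| Assumed shift | Rejection rate, 25 v 13 | Rejection rate, 28 v 14 |
|---|---|---|
| 0 | 5% | 5% |
| 0.2 SD | 8.8% | 9.2% |
| 0.3 SD | 13.7% | 14.6% |
| 0.5 SD | 29.6% | 32.0% |

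The same calculation shows masking. A true difference of 0.8 SD is detected with power 62.4% (25 v 13) or 66.5% (28 v 14). An opposing shift of 0.3 SD leaves a net 0.5 SD, and the chance of detection falls to the last row, 29.6% or 32.0%.

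**5. What randomising would not change.** The 62-66% power is the same with or without it. So is the 95% confidence interval half-width, 2.03 × 0.342 = 0.69 SD at 25 v 13. Both follow from the arm sizes. Randomisation removes the systematic component only.

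**The case against.** The strongest case on the other side has several parts.

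- **The main result is randomised.** Study design defines suppression as second dose in one arm against first dose of the same vaccine in the other, and the sample size is built on that comparison. This stands. A reader might infer that the primary objective as a whole is compromised. The documents do not support that: only its contrasts with Arm 3 are exposed.
- **Arm 3 is not the only safeguard against an antibody explanation.** The two live vaccines carry different prM and E proteins, PRNT against both viruses is planned on Days 0, 28 and 58, and anti-NS1 antibody is measured repeatedly. Arm 3 is introduced as an addition, with a note that earlier work saw no suppression of YF17D RNAemia by inactivated JEV. This stands too, so it would go too far to say that the T-cell conclusion rests on Arm 3 alone. The sponsor nevertheless names Arm 3 as the control.
- **Differences in time, lot or batch are not documented.** A separate cohort need not be a later one. The YF17D content of 4.0 to 5.8 log PFU is the product's range and no evidence that the arms receive different lots. Eligibility, site and schedule are common to all arms, and the endpoint is a laboratory assay. These biases are therefore open possibilities. The common criteria and site reduce selection bias but do not exclude it.
- **There may be a reason that the article omits.** A condensed article can leave out operational grounds, so one can say only that no benefit is stated. The intramuscular route of the inactivated vaccine may explain open-label dosing. It does not prevent random allocation.
- **Randomisation would not give a pure antibody contrast.** The primes in Arms 1 and 3 would still differ in live versus inactivated vaccine and in route. That is correct. It would still let a difference be attributed to the priming regimen, which the present design does not.

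**Conclusion.** The point holds, confined to contrasts with Arm 3. The control named in the primary objective is a separate, non-randomised cohort by the plan's own statement, and no reason is given. Arm 1 versus Arm 3 after challenge, and Arm 3 Day 28 versus Arm 2 Day 0, are open to selection bias and conditionally to time, lot and batch bias. The powered comparison between Arms 1 and 2 is sound in this respect.

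If the non-causal shift were 0.2 to 0.5 SD, the nominal 5% error of Arm 1 versus Arm 3 would be about 9% to 32%. This rests on assumed shifts and, for the lower figures, on 10% drop-out in Arm 3. It shows sensitivity and does not estimate the bias present. The design is openly labelled, so nothing is misreported. What makes the point worth raising is that the planned sizes already fit a 2:2:1 randomisation.

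**What to change.** Randomise all 70 subjects concurrently 2:2:1 (28:28:14) from one allocation list covering the three arms, concealed until each subject is assigned. Keep Arms 1 and 2 double-blind and Arm 3 open-label after allocation. The total, the arm sizes and the power of the comparison between Arms 1 and 2 do not change. The cost is an amendment to the randomisation and consent text (70 allocations in place of 56), and the option to recruit Arm 3 as a stand-alone cohort is lost.

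If recruitment is too far advanced, keep Arm 3 as it is and state the reason for the separate cohort. Label every contrast with Arm 3 as non-randomised supportive evidence and report it as an estimate with a 95% confidence interval. Do not read p > 0.05 as absence of an antibody effect: with a half-width of about 0.69 SD, such a result leaves sizeable effects possible. Do not switch partway and pool randomised with non-randomised Arm 3 subjects without distinguishing them.

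### Both suppression estimates are total priming effects: Arm 3 can separate out antibody for the YF17D challenge only, and JE-YF17D suppression in Arm 2 has no antibody-control arm

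*Protocol article*

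**What the plan says.** Hypothesis and objectives states that the goal is to "define a minimum quantitative threshold of T cells induced by vaccination needed to control subsequent infection, independent of antibodies". The same section gives inactivated JEV vaccine its role: "to control for the effects of cross-reactive anti-flaviviral antibodies, although we have not observed suppression of YF17D RNAemia from inactivated JEV vaccination". It also argues that the two live vaccines carry different prM and E proteins, so that neutralizing antibody to one should not protect against the other.

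Study design then defines the effect. For JE-YF17D, "the level of suppression of JE-YF17D RNAemia will be the difference in RNAemia levels between subjects who received JE-YF17D as a second vaccination (Arm 2" is one side of the comparison, and the other side is given as "compared to those who received it as a first vaccination (Arm 1), and similarly for YF17D vaccine". The reference is described only by its lack of T cells: "The first vaccination in Arms 1 and 2 would provide the RNAemia response in the absence of virus-specific T cells". Sample size calculation powers the same second v first dose contrasts.

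On the control arm, Study design says: "A separate non-randomized non-blinded cohort of 14 subjects will be recruited into Arm 3". It adds: "Subjects in Arm 3 will receive inactivated JEV vaccine (IXIARO^®^, Valneva) on Day 0 followed by YF17D vaccine on Day 28". It calls Arm 3 the control arm because no YF17D-specific T-cell response is expected there. The primary objective names the inactivated JEV group among the three groups compared after challenge.

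**The concern.** A subject receiving a live vaccine on Day 28 differs from a naive first-dose recipient in more than T cells. Antibody from the Day 0 vaccine is also present, and so is any other effect of prior vaccination. A difference between these two states cannot by itself be credited to T cells. The protocol recognises this by including an arm for cross-reactive antibody, but the definition of suppression does not use that arm, and the arm meets only one of the two challenge viruses.

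What is at stake is the trial's main inference. If the second v first dose differences are read as T-cell suppression, an antibody-independent conclusion would rest on contrasts that do not separate the two arms of immunity. This matters most in Arm 2, where Study design expects the stronger suppression.

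**Working it through.** **1. What differs between the groups at the measured dose.** Allocation is from Table 1. Naive status is from Study population. The shared backbone is from Hypothesis and objectives. That inactivated JEV induces no antibody to YF17D NS1 is an assumption.

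| Dose measured | Group | Backbone T cells | Structural antibody from Day 0 | Antibody to YF17D NS1 |
|---|---|---|---|---|
| YF17D | Arm 2, Day 0 | none | none | none |
| YF17D | Arm 1, Day 28 | expected | JE | possible |
| YF17D | Arm 3, Day 28 | not expected | JE | not expected |
| JE-YF17D | Arm 1, Day 0 | none | none | none |
| JE-YF17D | Arm 2, Day 28 | expected | YF | possible |
| JE-YF17D | antibody without backbone T cells | no such arm (0 subjects) | | |

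**2. What each contrast estimates.** Write T for the T-cell effect, A for structural cross-reactive antibody, N for antibody to the shared NS1, and O for other effects of prior vaccination.

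- YF17D, Arm 1 Day 28 v Arm 2 Day 0: T + A(JE) + N + O.
- JE-YF17D, Arm 2 Day 28 v Arm 1 Day 0: T + A(YF) + N + O.
- YF17D, Arm 1 Day 28 v Arm 3 Day 28: A(JE) cancels if the Day 28 JE titres are similar. T, N and any live v inactivated difference in O remain, plus confounding because Arm 3 is not randomised.

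No planned contrast removes A(YF) from the second line.

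**3. The plan's own sample size.** Inputs from Sample size calculation: 0.8 SD, 80% power, two-sided 5%, 10% drop-out.

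- Normal approximation: n = 2(1.960 + 0.842)² / 0.8² = 24.5, so 25 per group, with 80.7% power at 25.
- Exact t-test: 25.5, so 26 per group, with 79.1% power at 25.
- Drop-out: 25 / 0.9 = 27.8, so 28.

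The stated 25 and 28 reproduce, so the arithmetic is not at fault.

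**4. Precision of Arm 1 v Arm 3.** In the normal approximation, power = Φ(0.8 × √(n1·n3/(n1+n3)) − 1.960). For 28 v 14 this is Φ(0.8 × 3.055 − 1.960) = Φ(0.484) = 69%. With 10% drop-out, 28 × 0.9 = 25.2 and 14 × 0.9 = 12.6, so the contrast becomes 25 v 12 or 13.

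| n (Arm 1 v Arm 3) | Power at 0.8 SD, normal | Power at 0.8 SD, t-test | Detectable at 80% (t-test) |
|---|---|---|---|
| 28 v 14 | 69% | 66% | 0.94 SD |
| 25 v 13 | 65% | 62% | 0.98 SD |
| 25 v 12 | 62% | 60% | 1.01 SD |

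With 25 evaluable in Arm 1, 80% power would need 25 (normal) to 27 (t-test) evaluable in Arm 3.

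**The case against.** The protocol gives reasons for its reference group. It holds that neutralizing antibody is type-specific, and it reports that inactivated JEV did not suppress YF17D RNAemia. If both are right, A(JE) is zero or near it, and the YF17D estimate loses little. That stands, and it is why the bias may be zero in that direction. But the observation concerns JE antibody before YF17D, not YF17D antibody before JE-YF17D. The type-specificity argument rests on prM and E, so it does not reach NS1, which both live vaccines share.

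A reader might infer that Arm 3 plays no part in the trial. The documents do not support that. The primary objective includes the inactivated JEV group, and Arms 1 and 3 receive the same challenge on the same day. The gap is narrower: that contrast is absent from the definition of suppression and from the power statement.

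A reader might also infer that nothing could separate antibody from T cells in Arm 2. Table 2 schedules PRNT and anti-NS1 before the Day 28 challenge, so the data for an adjustment will exist. Covariate choice is commonly left to an analysis plan, which is not shown, so its absence from the article is not an error. An analysis plan cannot, however, supply the missing arm.

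Finally, one could assume an antibody effect of 0.1 to 0.4 SD and report that 0.1/0.8 = 12.5% to 0.4/0.8 = 50% of the planned effect is misattributed. The documents give no basis for that range, and their one observation is of no effect. Any such range must include zero.

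**Conclusion.** The point holds in a limited form. Both suppression estimates, as defined, are total priming effects. One of them can be set beside an antibody-control arm that its definition leaves out. The other, JE-YF17D in Arm 2 (28 of the 56 randomised subjects), has no antibody-control arm. The first two statements follow from the definition and from naive status at entry, and the third from Table 1; none needs a numerical assumption.

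The size of any misattribution cannot be derived from the documents. The available control contrast suits estimation rather than a confirmatory test: 60-62% power at 0.8 SD after drop-out, in a non-randomised, open-label comparison. These figures assume that the plan's 10% drop-out also applies to Arm 3. The text does not show that antibody causes the suppression, only that the defined contrasts cannot exclude it.

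**What to change.** In Study design and Sample size calculation:

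- Keep the randomised second v first dose contrasts as the powered comparisons, and label both as total priming effects.
- Name Arm 1 Day 28 v Arm 3 Day 28 as the antibody-controlled YF17D contrast. Report an estimate with a confidence interval. State that it is non-randomised and open label, with about 60-62% power at 0.8 SD after drop-out (detectable effect 0.98-1.01 SD).
- Compare Day 28 JE-YF17D PRNT50 and anti-NS1 between Arms 1 and 3, since the control works only as far as JE titres are similar, and matching PRNT50 says nothing about NS1.

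For JE-YF17D in Arm 2:

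- Make no antibody-independent claim from the Arm 2 v Arm 1 difference alone.
- Add a sensitivity analysis of the post-challenge regression of peak RNAemia on T-cell response (Data and statistical analysis), with Day 28 PRNT50 and anti-NS1 as covariates.
- Do not restrict Arm 2 to subjects with undetectable PRNT50. That selects on a post-randomisation response, has no counterpart in the Arm 1 reference, and misses non-neutralizing antibody.

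The cost is wording, one stated contrast and one sensitivity analysis, all from samples already scheduled. The downside is real: the antibody-controlled contrast is less precise and open to confounding, and the Arm 2 conclusion becomes narrower.
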